| **Study Design** | This is a prospective, single-center, single-arm, phase II clinical study. This study plans to enroll 30 treatment-naïve and operable patients with locally advanced adenocarcinoma gastric. After signing the informed consent form, patients will be screened to ensure they meet the inclusion and exclusion criteria. Before surgery, patients will receive three cycles of neoadjuvant therapy with Serplulimab combined with the SOX regimen and nine weeks of thymalfasin. The efficacy of neoadjuvant therapy and the feasibility of radical D2 resection will be assessed via imaging after Cycle 2 and Cycle 3. Radical gastrectomy will be performed within 2–6 weeks after completing the third dose. The postoperative treatment of patients will be jointly decided by clinical physicians and patients according to the actual conditions of clinical diagnosis and treatment.  The main observation indicator is the pCR rate after neoadjuvant therapy;  Safety assessment: The safety will be assessed once after each cycle of neoadjuvant therapy and at 30 days after surgery;  Event follow-up: The events will be followed up every 3 months during the first year after surgery, and once every 6 months from the first to the second years, until the second year. |

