| Administration Method of the Study Drugs | Neoadjuvant therapy phase:  Serplulimab: 300 mg, i.v., D1, Q3W;  Thymalfasin: 4.8 mg, subcutaneous injection, twice a week. On Day 1 and Day 4 of each week during Weeks 1–9 or until surgery;  Oxaliplatin: 130 mg/m2, i.v., D1, Q3W;  Tegafur: oral administration: body surface area < 1.25 m^2^, 40 mg each time; body surface area ≥ 1.25 to < 1.5 m^2^, 50 mg each time; body surface area ≥ 1.5 m^2^, 60 mg each time, twice daily for each treatment cycle at D1-D14  After 3 courses of treatment before surgery, radical gastrectomy will be conducted based on evaluation by the investigator within 2–6 weeks after completion of chemotherapy + immunotherapy.  Adjuvant therapy phase: The postoperative treatment of patients will be jointly decided by clinical physicians and patients according to the actual conditions of clinical diagnosis and treatment. |
| **Evaluation Criteria** | Efficacy evaluation:  Evaluation per RECIST v1.1 criteria:   - Pathologic complete response (pCR) rate, defined as the proportion of subjects with no residual viable tumor cells under microscopic examination and negative lymph nodes among the total subjects; - Major pathologic response (MPR) rate, defined as the proportion of subjects with ≤10% viable tumor cells in the resected specimen among the total subjects; - Tumor regression grade (TRG) - Objective response rate (ORR), defined as the proportion of subjects achieving complete response (CR) and partial response (PR) among the total subjects; - Clinical downstaging rate: ypT0 ratio, ypN0 ratio, and preoperative imaging clinical stage will be counted, respectively, to compare with baseline imaging clinical stage downstaging ratio. - Disease-free survival (DFS), defined as the time from surgery to the first radiological disease recurrence or death (whichever occurs first); - Overall survival (OS), defined as the time from enrollment to death of the subject due to any cause;   Safety evaluation:   - Drug-related safety (per CTCAE 5.0): incidence, relationship to study drug and severity of TRAEs, TRAEs ≥ Grade 3, irAEs, etc. - Surgery-related safety (according to Dindo-Demartines-Clavien classification). |

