- Disease-free Survival (DFS): Disease-free survival refers to the time from the start of randomization to disease recurrence or death due to disease progression. DFS will be defined as the last date the patient is last confirmed to be disease-free survival if the patient does not experience disease progression during the study. Patients who discontinue the trial for reasons other than disease progression (no subsequent imaging) and patients who receive treatment after the trial will be censored at the time of discontinuation or the time of initiation treatment after the trial. When patients are not censored at the time of discontinuation from the trial or the time of initiation treatment after the trial, pre-planned sensitivity statistical analyses will further confirm DFS based only on the time of event of radiologically confirmed progression. New onset of other tumors are not considered as disease progression events and are not censored. If an imaging examination and evaluation show disease progression, the date of disease progression will not be the imaging examination date when disease progression is first shown, but the imaging examination date when disease progression is clearly confirmed. If disease progression is diagnosed by other clinical modalities, the date of diagnosis will be used as the date of disease progression.
- Overall Survival (OS): Overall survival refers to the date from enrollment to death due to any cause. For patients who are alive at last follow-up, their OS will be censored based on the time of last follow-up. For patients who are lost to follow-up, their OS will be censored based on the last confirmed survival time before loss to follow-up. The OS of data censor is defined as the time from enrollment to censoring.
- R0 resection rate: R0 resection rate refers to the proportion of patients who complete R0 resection in the total number of enrolled patients with surgically resectable gastric cancer through 3 cycles (21 days per cycle) of treatment with Serplulimab in combination with SOX regimen and 9 weeks of thymalfasin. Of these, R0 resection refers to negative microscopic margins.

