8. The surgery should be performed within Weeks 2–6 after the completion of the last chemotherapy + immunotherapy. The R0 resection rate of surgery in the overall patient population should be assessed. Tumor tissue from surgically resected specimens should be collected for immunofluorescence assay. Postoperative pathological specimens should be evaluated for pCR, MPR, and TRG (marking the conclusion of the study-related treatment). Blood tests such as hematology, blood biochemistry, urinalysis, and coagulation function should be completed within 3–7 days after surgery.

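### DFS is defined in two incompatible ways (start, qualifying deaths, event date), and section 2.2 does not say whether adjuvant therapy triggers censoring

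*Protocol*

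**What the plan says.** The Protocol defines DFS twice.

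- **Synopsis, Evaluation Criteria:** DFS is "defined as the time from surgery to the first radiological disease recurrence or death (whichever occurs first").
- **Section 2.2, Secondary Endpoints:** DFS is "the time from the start of randomization to disease recurrence or death due to disease progression".

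Section 2.2 adds dating and censoring rules that the synopsis lacks. For imaging, "the date of disease progression will not be the imaging examination date when disease progression is first shown"; the date is that of the scan on which progression is clearly confirmed. For other evidence, "If disease progression is diagnosed by other clinical modalities, the date of diagnosis will be used". On censoring, "patients who receive treatment after the trial will be censored at the time of discontinuation or the time of initiation treatment after the trial". Where that censoring is not applied, "pre-planned sensitivity statistical analyses will further confirm DFS based only on the time of event of radiologically confirmed progression".

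On design, the synopsis states: "This is a prospective, single-center, single-arm, phase II clinical study". Section 6.2 describes surgery and the pathology reading as "marking the conclusion of the study-related treatment", and the synopsis leaves postoperative treatment to the physician and the patient. Section 12.3 plans a Kaplan-Meier curve and a median DFS with 95% CI.

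**The concern.** These are not details that a later analysis plan could fill in. The Protocol fixes the endpoint in two places and the two do not agree.

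Section 2.2 starts the clock at an event that never occurs in this trial. It leaves out deaths not caused by progression, although such deaths after combined immunotherapy, chemotherapy and gastrectomy are part of what a reader expects DFS to capture. It also sets a later event date than the synopsis does.

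The censoring rule depends on an undefined term. Two analysts could both follow section 2.2 and keep either nearly all DFS events or very few, depending on whether they treat adjuvant therapy as post-trial treatment. If the choice is made after outcomes are known, the DFS result can be selected.

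**Working it through.** The Protocol gives no DFS rate or event count to reproduce. The first three steps compare the text; the fourth is an illustration.

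**1. Start.** Surgery (synopsis) against randomization (section 2.2). The design is single-arm, so no randomization date exists. If enrolment or first dose is meant instead, the origins differ materially. The third dose falls at week 2 × 3 = 6, and surgery follows 2-6 weeks later, at weeks 8-12 from first dose. If the 2-6 weeks run from the end of cycle 3 (week 9), surgery falls at weeks 11-15. The gap is roughly 2 to 3.5 months, plus any interval from enrolment to first dose.

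**2. Event.** Any death (synopsis) against death due to progression (section 2.2). Section 5.2 lists death as a withdrawal criterion, and section 2.2 censors those who discontinue for reasons other than progression, so a postoperative or toxic death would most naturally be censored. The Protocol gives no rate for such deaths. For scale, one death among the 6-15 events assumed in step 4 is 1/15 = 7% to 1/6 = 17% of all events. The two places also differ on non-radiological recurrence: the synopsis specifies radiological recurrence, while section 2.2 accepts clinical diagnosis.

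**3. Date.** First radiological recurrence (synopsis) against the confirming scan (section 2.2). The confirming scan cannot precede the first, so this rule leaves DFS unchanged or lengthens it. The shift is zero if the first scan is conclusive. It is at most about one visit interval if confirmation waits for the next scheduled visit: 3 months in year 1 and 6 months in year 2 (section 6.3).

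**4. Censoring, if adjuvant therapy counts as post-trial treatment.**

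- From the Protocol: N = 30; follow-up 2 years (104 weeks).
- Assumed: all 30 resected; exponential DFS from surgery; 2-year DFS S = 50%, 65% or 80%; adjuvant start at w = 4 to 12 weeks; share p receiving it = 100% or 70%.
- The 4-12 weeks come from flow-chart note 16, where they attach to the postoperative scan before adjuvant therapy, so they are a proxy for its start.

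With λ = −ln(S)/104:

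- events without this censoring = 30 × (1 − S)
- events kept with it = 30p × (1 − exp(−λw)) + 30(1 − p) × (1 − S)

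Example: S = 50%, w = 12, p = 100%. λ = 0.6931/104 = 0.00667, and 30 × (1 − exp(−0.0800)) = 2.3, against 30 × 0.5 = 15.

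| 2-year DFS | Events, no such censoring | Kept, all 30 treated (4 / 12 wk) | Kept, 70% treated (4 / 12 wk) |
|---|---|---|---|
| 50% | 15.0 | 0.8 / 2.3 (5% / 15%) | 5.1 / 6.1 (34% / 41%) |
| 65% | 10.5 | 0.5 / 1.5 (5% / 14%) | 3.5 / 4.2 (33% / 40%) |
| 80% | 6.0 | 0.3 / 0.8 (4% / 13%) | 2.0 / 2.3 (33% / 39%) |

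Among patients given adjuvant therapy, exp(−λw) = 92-99% would be censored at its start. If adjuvant therapy is not meant, the events kept equal the second column and the loss is nil.

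**5. Does the planned sensitivity analysis repair this?** It lifts the censoring but counts only radiologically confirmed progression. It therefore drops deaths and clinically diagnosed recurrence. No analysis described in section 2.2 gives the DFS of the synopsis.

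**The case against.** A reader might infer that almost every patient given adjuvant therapy will be censored weeks after surgery. The Protocol does not establish that. Section 6.2 ends study-related treatment at surgery, not the trial, which continues through two years of follow-up. Section 6.3 records adjuvant regimens and their duration within that follow-up, and the synopsis gives adjuvant therapy its own phase. On the other side, the flow chart has a follow-up row for subsequent anti-tumor treatment, which with section 6.2 makes the wider reading plausible. The term is ambiguous, and the share of patients given adjuvant therapy is stated nowhere. This objection stands, so the event loss is conditional.

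A reader might also blame the censoring rule for an unusable median. With 2-year DFS of 50-80% and 24 months of follow-up, the median would not be reached even without that rule, except exactly at 24 months in the 50% case. Nor is strong bias shown: if nearly everyone were censored at a similar early time, the censoring would be close to administrative, and the main harm would be lost information.

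The full 3- or 6-month dating shift is a worst case, because note 16 allows extra tumor assessments as clinically needed. Finally, DFS is one of several secondary endpoints in a small trial analysed mainly descriptively.

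None of this removes the three direct contradictions on start, qualifying deaths and dating.

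**Conclusion.** The two DFS definitions are incompatible, and the one in section 2.2 is wrong as written: its start does not exist in this design, it omits deaths not due to progression, and its dating rule moves DFS only upward, by zero up to one visit interval. These conclusions rest on the text alone.

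The effect of the censoring rule depends on the undefined term and on the assumptions of an exponential DFS, 2-year DFS of 50-80% and adjuvant start at 4-12 weeks. About 0.3-2.3 of 6-15 expected events remain if all 30 patients receive adjuvant therapy and it counts; 33-41% remain if 70% receive it; nothing is lost if it does not count. The sensitivity analysis does not close the gap.

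The sponsor should fix this before the DFS data are examined. The primary pCR analysis is not affected.

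**What to change.** Use one definition in the synopsis and section 2.2: time from surgery to first recurrence or death from any cause, dated at the first scan or clinical diagnosis that shows it. Remove the reference to randomization. State that postoperative adjuvant therapy is not a censoring event, and define what new therapy means. Make the analysis without that censoring the main one, and keep censoring at new therapy as a sensitivity analysis only.

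The cost is a wording change in two places. Section 6.3 already collects recurrence and adjuvant treatment, and survival status is in the flow chart, so no new data or additional endpoint is needed.

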
1. **Background**

Gastric cancer (GC) is a primary malignant tumor of epithelial origin in the stomach. Among malignant tumors worldwide, gastric cancer has the third highest mortality rate, and in China, the incidence of gastric cancer ranks second only to lung cancer, and the mortality rate ranks third. In the world, there are about 1.2 million new cases of gastric cancer each year, and China accounts for about 40% of them. The proportion of early-stage gastric cancer in China is very low, only about 20%. Most cases are already in the advanced stage when they are detected, with a proportion as high as 50%–60%, and the overall 5-year survival rate is less than 50%. At present, radical surgery is still the only way to cure gastric cancer, but the surgical resection rate is low, and the R0 resection rate is about 70–80%; patients with stage II or higher have a high postoperative recurrence rate. Therefore, increasing the surgical resection rate and seeking other treatments that are more effective other than surgical treatment are the development direction of gastric cancer treatment research.

Neoadjuvant therapy can reduce tumor stage and increase the likelihood of complete tumor resection to achieve maximum pathological response. Today, the role of neoadjuvant therapy in potentially resectable gastric cancer is gradually being recognized. The results of a large multicenter MAGIC study from Europe showed that patients with potentially resectable gastric cancer who underwent surgery after neoadjuvant chemotherapy had a higher R0 resection rate (79.3% vs. 70.3%, P < 0.05), overall survival, progression-free survival, and 5-year survival rate (36% vs. 23%, P < 0.05) compared with patients who underwent surgery alone. The results of the FNCLCC/FFCD phase III clinical trial also showed that patients with resectable gastric cancer who underwent surgery after neoadjuvant chemotherapy were significantly better than those in the surgery alone group in terms of R0 resection rate (84% vs. 73%, P = 0.04), overall survival (P = 0.02), progression-free survival (P = 0.003), and 5-year survival rate (38% vs. 24%, P = 0.02). Both studies demonstrated the efficacy and safety of neoadjuvant chemotherapy for gastric cancer, and served as the key evidence for the inclusion of neoadjuvant chemotherapy in combination with surgical treatment in the NCCN guidelines for the diagnosis and treatment of gastric cancer.

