Through reviewing its mechanism of action, thymalfasin is an immunological peptide with 28 amino acids, which has potential therapeutic effects on patients with various tumors (such as liver cancer, lung cancer, and lymphoma) and diseases (including infectious diseases and chronic hepatitis B), as well as immune improvement effects (*e.g.*, enhancing the response to vaccine) on patients with immunologic inadequacy. It mainly acts on Toll-like receptor 2 (TRL2) and TRL9 on dendritic cells (DCs), and stimulates intracellular signaling pathways including the NF-κB and p38 MAPK pathways, thus increasing the activity of natural killer (NK) cells. Moreover, it promotes the conversion of helper T (Th) cells to Th1 subset, increases the expression of Th1-type cytokines like IL-2 and IFN-γ, elevates the level of cytotoxic T lymphocytes (CTLs), and facilitates DC activation. Tumor cells can be killed through the combined action of NK cells, cluster of differentiation 4 (CD4)^+^ Th1 cells and CTLs. Meanwhile, activated DCs can also generate anti-tumor responses and perform efficient antigen presentation.

Based on the above background and basis, we designed this study to investigate the efficacy and safety of Serplulimab in combination with thymalfasin and SOX regimen for neoadjuvant therapy of locally advanced gastric cancer, and look forward to exploring safer and more effective neoadjuvant regimens for such patients to further benefit patients with gastric cancer.

1. **Objectives and Endpoints**
   1. **Objectives**
2. Primary objective: To investigate the efficacy and safety of Serplulimab in combination with thymalfasin and SOX regimen for neoadjuvant therapy of locally advanced gastric cancer.
3. Secondary objective: To investigate the effect of neoadjuvant therapy with Serplulimab in combination with thymalfasin and SOX regimen on tumor immune micro-environment in locally advanced gastric cancer.
   1. **Endpoints**
      1. **Primary Endpoint**

- Pathological Complete Response (pCR): For patients with surgically resectable gastric cancer after neoadjuvant therapy, the proportion of patients with no residual tumor cells in the primary site to the total enrolled patients.
  - 1. **Secondary Endpoints**
- Major Pathological Response (MPR): For patients with surgically resectable gastric cancer after neoadjuvant therapy, the proportion of patients with less than 10% residual tumor cells in the primary site to the total enrolled patients.

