Preoperatively, 3 cycles of Serplulimab in combination with SOX regimen and 9 weeks of thymalfasin neoadjuvant therapy were administered. Patients underwent imaging examinations after the second and third cycles of neoadjuvant therapy to assess efficacy and the possibility of undergoing radical surgery, and underwent surgery within weeks 2 to 6 from the completion of the third dose. Samples of surgically excised gastric tumor tissues were collected for immunofluorescence. Assessment of postoperative pathological findings included pCR, TRG, MPR, ORR, DCR, clinical downstaging rate and R0 resection rate. Patients' adverse reactions were assessed throughout the neoadjuvant therapy period to test the safety of neoadjuvant immunization combined with chemotherapy. Patients were followed up after surgery and DFS and OS were calculated. In addition, the immune cell infiltration of tumor tissues before and after neoadjuvant therapy was explored to investigate its relationship with the effectiveness of immunotherapy + thymalfasin + SOX.

All eligible subjects received neoadjuvant therapy, which was a neoadjuvant regimen of Serplulimab in combination with thymalfasin and SOX.

- Serplulimab: 300 mg, i.v., D1, Q3W;
- Oxaliplatin: 130 mg/m2, i.v., D1, Q3W;
- Tegafur: oral administration: body surface area < 1.25 m^2^, 40 mg each time; body surface area ≥ 1.25 to < 1.5 m^2^, 50 mg each time; body surface area ≥ 1.5 m^2^, 60 mg each time, twice daily for each treatment cycle at D1-D14;
- Thymalfasin: 4.8 mg, subcutaneous injection, twice a week. On Day 1 and Day 4 of each week during Weeks 1 ~ 9;

After the 2nd treatment course of Serplulimab+SOX and after completion of the 3rd dose before surgery, the investigator will perform 2 assessments to assess whether radical gastrectomy is feasible, and if surgical treatment is feasible, it will be performed within 2-6 weeks after the 3rd dose.

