**Study Design Diagram**

**
[figure not shown]
**

1. **Selection Criteria for Subjects**
   1. **Study Population**

cStage III gastric/gastroesophageal junction adenocarcinoma

- 1. **Inclusion Criteria**

1. Male or female patients aged 18–75 years with G/GEJ adenocarcinoma;
2. According to the AJCC 8th edition gastric cancer staging, patients with cStage III (cT_3-4a_N_1-3_M_0_) assessed by abdominal CT and G/GEJ adenocarcinoma diagnosed by gastroscopy and pathology (HER-2 negative or 1+); and patients with gastroesophageal junction (GEJ) cancer will only allow Siewert type III, and Siewert type II subjects who do not require combined thoracotomy to be enrolled.
3. Before enrollment, a doctor in charge of gastrointestinal surgery and an imaging technician jointly assess that the tumor is cStage III and qualified for the study of R0 resection with the purpose of cure, and the patient agrees to receive radical surgery and has no contraindication to surgery as judged by the surgeon;
4. No previous systemic therapy for the current disease, including surgical treatment, anti-tumor chemoradiotherapy/immunotherapy;
5. Expected survival of ≥3 months;
6. There are measurable tumor lesions according to RECIST v1.1 (see Attachment 3 for details);
7. ECOG PS score (see Attachment 4 for details) of 0–1 within 7 days after the first dose;
8. The heart is functioning well and resection for curative purposes can be performed. Patients with underlying ischaemic, valvular or other significant cardiac disease should be evaluated preoperatively by a cardiologist, if clinically indicated;
9. Primary organs are functioning normally and subjects are required to meet the following laboratory parameters:
   1. Absolute neutrophil count (ANC) ≥ 1.5 × 10^9^/L in the absence of granulocyte colony-stimulating factor in the past 14 days;
   2. Platelets ≥ 100 × 10^9^/L without transfusion in the past 14 days;
   3. Hemoglobin > 9 g/dL without or erythropoietin use within the past 14 days;
   4. Total bilirubin ≤ 1.5 × upper limit of normal (ULN); if total bilirubin > 1.5 × ULN but direct bilirubin ≤ ULN, the patient is also allowed to be enrolled;
   5. Aspartate aminotransferase (AST) and alanine aminotransferase (ALT) ≤ 2.5 × ULN
   6. Serum creatinine ≤ 1.5 × ULN and creatinine clearance (calculated using the Cockcroft-Gault formula) ≥ 60 ml/min;
   7. Good coagulation, defined as international normalized ratio (INR) or prothrombin time (PT) ≤ 1.5 times ULN;

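### The R0 denominator in Section 2.2 can be read as limited to patients who stay resectable through all three cycles, and it is not reconciled with Section 6.2 or with the pCR and MPR denominator

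*Protocol*

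**What the plan says.** In the protocol, Section 2.2 (secondary endpoints) takes the R0 resection rate as the share of patients with R0 resection "in the total number of enrolled patients with surgically resectable gastric cancer through 3 cycles (21 days per cycle) of treatment" with Serplulimab plus SOX and 9 weeks of thymalfasin. R0 itself is defined there as negative microscopic margins.

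Section 6.2, item 8, describes the same quantity without either qualifier: "The R0 resection rate of surgery in the overall patient population should be assessed".

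For pCR, Section 2.2 opens with a resectability clause, "For patients with surgically resectable gastric cancer after neoadjuvant therapy", but then closes with an explicit denominator: "the proportion of patients with no residual tumor cells in the primary site to the total enrolled patients". MPR is built the same way.

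Resectability is also an entry condition. Inclusion item 3 requires the surgeon and the imaging specialist to "jointly assess that the tumor is cStage III and qualified for the study of R0 resection with the purpose of cure", and the Synopsis states: "This study plans to enroll 30 treatment-naïve and operable patients with locally advanced adenocarcinoma gastric".

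Section 3 makes surgery conditional on assessment after treatment: "if surgical treatment is feasible, it will be performed within 2-6 weeks after the 3rd dose". Section 5.1 does not treat progression as study termination if the patient remains eligible for radical resection and has completed at least one cycle.

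**The concern.** The two qualifiers in the R0 definition, resectable disease and three cycles, sit on the denominator itself. If they restrict it, membership depends on what happens after treatment starts. Patients who progress to unresectable disease, die or stop for toxicity would drop out, although these are ways in which the regimen can fail to deliver an R0 resection. The protocol expects that such patients may occur: Section 5.1 lists intolerable toxicity and progression to unresectability as reasons to terminate, and the safety endpoint in Section 2.2 counts patients made inoperable by treatment-related events.

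Two analysts following the protocol could therefore report two different R0 rates from the same data. The Background gives a better chance of complete resection as a purpose of neoadjuvant therapy, so readers of a single-arm study will look at this rate.

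**Working it through.** The protocol states no R0 target, no R0 hypothesis and no expected number of unresected patients, so there is no figure of its own to reproduce. What follows is an illustration.

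**Inputs**
- N = 30 enrolled (Synopsis, Study Design).
- x = number of R0 resections. Assumed 24 or 21, which are 80% and 70% of 30. These are the ends of the general range of 70–80% in the Background, which is not a design assumption.
- k = number of non-R0 patients removed by the qualifiers. Not given; assumed 0 to 6.

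**Step 1. Only non-R0 patients leave.** The all-enrolled rate is x/30 and the restricted rate is x/(30−k). Their ratio is 30/(30−k), whatever x is.

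| k | 30/(30−k) | x = 24 | x = 21 |
|---|---|---|---|
| 0 | 1.000 | 80.0% | 70.0% |
| 1 | 1.034 | 82.8% | 72.4% |
| 2 | 1.071 | 85.7% | 75.0% |
| 3 | 1.111 | 88.9% | 77.8% |
| 4 | 1.154 | 92.3% | 80.8% |
| 5 | 1.200 | 96.0% | 84.0% |
| 6 | 1.250 | 100% | 87.5% |

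For x = 24 and k = 3 the exact (Clopper-Pearson) 95% intervals are 61.4–92.3% for 24/30 and 70.8–97.6% for 24/27. The last x = 24 entry requires every non-R0 patient to be a dropped patient, with no R1 resection among completers, so it is the extreme of the range.

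**Step 2. Patients with R0 leave as well.** Section 5.1 leaves room for surgery after fewer than three cycles. A strict three-cycle condition would remove such patients from numerator and denominator. If m patients are removed in all and j of them had R0, the restricted rate is (24−j)/(30−m). It exceeds 24/30 when 30(24−j) > 24(30−m), that is, when j/m < 0.8.
- m = 3, j = 0: 24/27 = 88.9% (up).
- m = 6, j = 3: 21/24 = 87.5% (up; j/m = 0.5).
- m = 3, j = 3: 21/27 = 77.8% (down; j/m = 1).

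The rate rises when those removed have a lower R0 proportion than the whole group, and falls when they have a higher one.

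**Step 3. The two readings side by side.**
- All enrolled: resectability describes everyone at entry, and the three cycles name the treatment given. Section 2.2 then agrees with Section 6.2, and k = 0.
- Restricted: resectability and three cycles are conditions to be met by the end of treatment. Section 2.2 then conflicts with Section 6.2 and departs from the pCR and MPR denominator.

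No section says which reading governs.

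**The case against.** The strongest reply is that the R0 sentence speaks of the total number of enrolled patients and that everyone enrolled is resectable at entry, so it may simply describe the trial population. The pCR and MPR definitions support this: they carry a more explicit post-treatment resectability clause and still divide by all enrolled, so such phrases in this protocol do not reliably restrict a denominator. This stands, and it is why the point is one of ambiguity. It does not remove the problem. For pCR and MPR an explicit denominator closes the sentence, while for R0 the qualifiers are attached to the denominator, where they would be redundant if they only restated eligibility.

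A reader might go further and infer that the protocol restricts R0 to patients still resectable, and that the reported rate is therefore inflated. The documents do not support that. The restriction is one of two readings, and Step 2 shows that the direction depends on who is dropped.

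A reader might also set the illustrative rates against the 79.3% and 84% that the Background quotes from earlier trials. The Background words these as rates in patients who had surgery after neoadjuvant chemotherapy, the denominators of those trials cannot be seen here, and the protocol plans no such comparison.

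Finally, Section 12.1 provides a full analysis set that requires neither resectability nor three cycles, and R0 is one of several secondary endpoints in a mainly descriptive analysis. Both are true and limit the weight of the point. But the analysis sets do not override a denominator written into the endpoint definition.

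**Conclusion.** The concern holds as an unresolved denominator. Section 2.2 can be read as limiting the R0 rate to patients who remain resectable through the full course, and this is not reconciled with Section 6.2, item 8, or with the denominator of pCR and MPR.

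Under the restricted reading, and if only non-R0 patients leave, the rate rises by the factor 30/(30−k): 8.9 percentage points for the assumed 24 R0 resections and k = 3. If only patients with R0 after fewer than three cycles leave, three such patients lower it by 2.2 points (80.0% to 77.8%). Under the all-enrolled reading there is no effect. All counts are assumptions, so the size in this trial cannot be stated. The primary pCR analysis is not affected.

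**What to change.** In Section 2.2, define the R0 resection rate as the number of patients with R0 resection divided by all enrolled patients, the same denominator as pCR and MPR. Delete the resectability and three-cycle qualifiers from that sentence. State that patients without surgery count as not R0. Use one population throughout and do not mix enrolled with treated patients. Section 6.2, item 8, can then stand as it is.

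Report R0 among resected patients only as a supplementary figure, labelled as such, with its own denominator shown.

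The change is to wording only and adds no patients, visits or assessments. The price is that the R0 rate may look less favourable.
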